## Background

Septic shock, a critical condition characterized by organ failure, presents a substantial mortality risk in intensive care units (ICUs), with the 28-day mortality rate possibly reaching 40% [1]. The conventional management of septic shock typically entails antibiotics, supportive organ care, and surgical interventions as needed. In recent decades, researchers have explored extracorporeal blood purification therapies (EBPT) as supplementary treatments for immunomodulation during septic shock, including methods like high-volume hemofiltration (HVHF), the use of high cut-off (HCO) membranes, adsorption techniques, and plasmapheresis [2]. However, the clinical effectiveness of these EBPT technologies remains a topic of debate, necessitating verification through multicenter randomized controlled trials (RCTs). Septic shock frequently leads to acute kidney injury (AKI), impacting a significant portion of patients afflicted by this condition [3, 4]. Critically ill patients with sepsis-associated AKI who require renal replacement therapy (RRT) face an increased risk of mortality [3, 5, 6]. A novel approach, sequential extracorporeal therapy in sepsis (SETS) [7–9], has been proposed for multiple organ dysfunction syndrome (MODS) arising from endotoxic or septic shock. SETS envisions extracorporeal therapies serving as broad-spectrum support, sequentially replacing or supporting the function of multiple organs such as the heart, kidneys, liver, and lungs. Despite numerous studies, decisions about initiating EBPT or RRT in septic shock patients often rely on local clinical practices and the attending physician’s judgment. The optimal timing, modality, duration, and anticoagulation strategies for these therapies remain unclear. Particularly, in the Italian context, there remains a notable scarcity of high-quality data regarding the utilization of RRT and EBPT. Given this deficiency, this study aims to examine and describe the utilization of EBPT in septic shock patients, investigating any potential association between EBPT utilization and 90-day mortality. The study will also offer insights into EBPT utilization based on the presence of AKI in the context of septic shock in Italy.

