##### Secondary outcome

To assess association between EBPT and 28-day and 90-day mortality in patients with septic shock.To assess the proportion of EBPT utilization in septic patients, according to the presence/absence of AKI.To describe indication, modality, and duration of EBPT in septic patients, also according to the presence/absence of AKI.\To assess proportion, indication, modality, and duration of SETS in septic patients with renal failure.To assess association between SETS utilization and 90-day mortality in septic patients with renal failure.To describe changes in blood lactate, vasoactive inotropic score (VIS), Sequential Organ Failure Assessment (SOFA) score, and AKI staged (with KDIGO criteria) before and after starting EBPT and SETS.To evaluate relationship between 90-day mortality and changes in blood lactate, VIS, SOFA score, and AKI staged (with KDIGO criteria) in patients undergoing EBPT and SETS.To evaluate relationship between fluid accumulation at EBPT initiation and 90-day mortality.To assess the frailty score change at 28- and 90-day post-discharge.To identify possible risk factors (e.g., baseline clinical parameters, features of EBPT) for 90-day mortality in patients with EBPT or SETS.To investigate the impact of time of EBPT and SETS on renal outcomes, mortality, ICU and hospital length of stay, and 28-day free EBPT (free-SETS days).

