### Statistical analysis plan

All parameters will be described by frequencies (absolute and relative) and mean (SD) or median (IQR) based on data distribution. EBPT and SETS will be described in terms of indication, modality, and timing. Differences between patients undergoing and not undergoing EBPT will be assessed using the chi-square test (for discrete variables) or Student’s *T*-test (for continuous variables). Continuous variables not normally distributed will be compared using appropriate nonparametric tests (such as Wilcoxon’s sign test). Similar tests will be conducted to compare patients alive at discharge (from ICU and from hospital) versus those who did not survive, as well as patients with and without AKI (according to KDIGO criteria).

For patients undergoing EBPT or SETS, paired tests (paired *t*-test, Wilcoxon signed-rank test) will be applied to assess statistical differences in lactates, VIS, SOFA score, and AKI stage (based on KDIGO criteria) before and after EBPT or SETS. Multivariable generalized linear regression models will be performed to investigate the association between clinical outcomes (renal outcomes, mortality, ICU and hospital length of stay, free days from EBPT or SETS) and demographic/clinical variables in patients undergoing EBPT or SETS. Depending on the number of participating centers, the characteristics of the centers collected in the case report form may be included in the list of predictor variables for the models.

Relationships will also be analyzed using survival analysis (Kaplan–Meier approach and Cox proportional hazard models) to account for failure time and censoring data. EBPT utilization will be reported in terms of absolute risk and 95% confidence levels. Absolute risk will also be estimated for patients with and without AKI. Estimates will be used to assess the risk ratio for mortality (at 28 days and 90 days) in the entire population and stratified according to the presence or absence of AKI. The same approach will be used to assess SETS utilization in the ICU. All hypothesis tests will be two-sided, and *P* < 0.05 will be considered to indicate statistical significance.

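### ICU and hospital stay is to be fitted with generalized linear models that cannot tell early death from early discharge; analyse time to discharge alive, with death as a competing event

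*Protocol article*

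**What the plan says.** The Statistical analysis plan section of the protocol article states: "Multivariable generalized linear regression models will be performed to investigate the association between clinical outcomes". The outcomes it lists are "renal outcomes, mortality, ICU and hospital length of stay, free days from EBPT or SETS", and the models are fitted in patients who received EBPT or SETS. No distribution family, link or rule for patients who die is given.

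The Secondary outcome section makes this a named objective. The timing of EBPT and SETS is to be related to renal outcomes, mortality, "ICU and hospital length of stay, and 28-day free EBPT (free-SETS days").

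For changes around treatment, "paired tests (paired *t*-test, Wilcoxon signed-rank test) will be applied to assess statistical differences in lactates, VIS, SOFA score, and AKI stage".

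A later sentence adds: "Relationships will also be analyzed using survival analysis (Kaplan–Meier approach and Cox proportional hazard models) to account for failure time and censoring data". It does not say which outcomes this covers, or whether death is an event, a censoring or a competing event when the outcome is discharge.

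On expected mortality, the Background describes septic shock "with the 28-day mortality rate possibly reaching 40" percent.

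**The concern.** A stay in the ICU or hospital ends in one of two ways, discharge alive or death. They have opposite meanings but produce the same kind of number. A regression on days of stay, whatever its family or link, sees only the number. If deaths tend to come earlier than discharges, a factor that increases mortality shortens the average stay even when it does nothing for recovery.

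At stake is the secondary objective on EBPT and SETS timing. A timing pattern associated with more early deaths could be reported as associated with shorter stay and read as a benefit. The Discussion section says the study is meant to inform therapeutic decisions, so that misreading would matter.

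**Working it through.** The article gives no figure for stay, treatment duration or change in scores, so there is no stated result to reproduce. Every input below is an assumption except the 28-day mortality of up to 40% (Background), which the assumed values of 30% and 50% bracket.

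**1. Stay, fixed distributions.** Assume lognormal stay in survivors (median 12 days, sigma 0.7) and in non-survivors (median 5 days, sigma 1.0). The mean of a lognormal is median × exp(sigma²/2).

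- Survivors: 12 × exp(0.245) = 15.3 days.
- Non-survivors: 5 × exp(0.5) = 8.2 days.
- Overall mean at mortality m: (1 − m) × 15.33 + m × 8.24.
- m = 0.30: 10.73 + 2.47 = 13.2 days.
- m = 0.50: 7.67 + 4.12 = 11.8 days.
- The corresponding medians are about 9.9 and 8.4 days.

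The fall of 1.4 days is 0.20 × (15.33 − 8.24). It is zero if non-survivors stay as long as survivors, and it reverses if they stay longer.

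**2. Stay, constant hazards.** Assume discharge alive at 1/15 per day regardless of mortality. For mortality m the death hazard is (1/15) × m/(1 − m). The total hazard is then (1/15)/(1 − m), and mean stay is 15 × (1 − m).

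| Mortality | 20% | 30% | 40% | 50% | 60% |
|---|---|---|---|---|---|
| Mean stay (days) | 12.0 | 10.5 | 9.0 | 7.5 | 6.0 |

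The rate of discharge alive never changes, yet mean stay halves across the table. In this model the mean among survivors equals the overall mean, so restricting the regression to survivors does not remove the artefact.

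**3. What a competing-risk analysis shows under the same assumptions.** The probability of discharge alive by day 28 is (1 − m) × [1 − exp(−28/(15(1 − m)))].

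- m = 0.30: 0.70 × (1 − 0.069) = 0.65.
- m = 0.50: 0.50 × (1 − 0.024) = 0.49.
- One minus Kaplan–Meier with deaths censored: 1 − exp(−28/15) = 0.85 in both cases.

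Cumulative incidence shows the higher-mortality group doing worse. One minus Kaplan–Meier shows no difference and overstates discharge in both groups. A cause-specific Cox model for discharge would correctly return a hazard ratio of 1. It should be reported beside the hazard of death.

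**4. Free days.** Assume 3 days of EBPT and deaths uniform over 28 days.

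| Mortality | 30% | 40% | 50% |
|---|---|---|---|
| Mean free days, death ignored | 25.0 | 25.1 | 25.1 |
| Mean free days, only days alive count | 20.9 | 19.5 | 18.1 |
| Mean free days, death by day 28 scored 0 | 17.5 | 15.0 | 12.5 |

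The scoring rule decides whether the endpoint responds to mortality at all. The article does not state the rule.

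**5. Paired changes.** Both tests need a value before and a value after. In a simulation with true mean change zero, the after value was assumed to be missing more often in patients who worsen (log-odds 1 per SD). The mean change among those measured is −0.09 SD at 10% missing, −0.17 at 20%, −0.25 at 30% and −0.33 at 40%. The article does not give the time of the after measurement, so the fraction that applies is unknown.

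**The case against.** Several points on the other side are sound.

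- **Survival methods are planned.** A Cox model for discharge with deaths censored is a cause-specific hazard model, which is a legitimate choice. The objection to censoring deaths applies to reading one minus Kaplan–Meier as a probability of discharge, not to Cox regression as such. This stands. However, the article does not link the survival analyses to stay, and it adds them to the generalized linear models rather than replacing those models.
- **Mortality is in the same list of outcomes.** A factor that raises deaths should show this beside any shorter stay. That limits the harm, but it depends on the two results being read together, which the plan does not require.
- **Free days.** A reader might infer that days after death will count as free. The article does not say so; it leaves the endpoint undefined for deaths, and a condensed article may leave scoring to a fuller document. Even if death were ignored, the illustration is essentially flat across mortality and does not favour the group with more deaths.
- **Paired tests.** A reader might infer that improvements in lactate, VIS and SOFA are necessarily inflated by survivor selection. That is not shown. These are single-group comparisons, so they cannot favour one factor over another. The loss depends on an unstated measurement time. The Data collection section describes monitoring over 72 h, and patients with life expectancy under 24 h are excluded, so 28-day mortality may be the wrong yardstick for dropout. Scoring deaths as worst would also change the question being asked.

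**Conclusion.** The point holds for ICU and hospital stay. The article names a method for that outcome which cannot separate early death from early discharge, in a population where death is common. The direction of the distortion requires only that deaths come earlier than discharges. Its size cannot be derived from the documents. With mortality raised from 30% to 50%, the two illustrations give a fall in mean stay of 1.4 and 3.0 days with no change in survivors' stay (first) or in the rate of discharge alive (second). The cited mortality is for septic shock in general, not for EBPT or SETS patients or for death in hospital.

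It would go too far to say that the plan ignores death throughout or that its results are biased. For free days and paired changes the article is silent rather than wrong, and these call for clarification only. The mortality analyses and the primary outcome, the proportion receiving EBPT, are unaffected. This is an inexpensive improvement to a secondary analysis.

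**What to change.** **Main change.** Replace the generalized linear models for stay with an analysis of time to discharge alive, treating death as a competing event:

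- report cumulative incidence of discharge alive and of death, instead of one minus Kaplan–Meier;
- use cause-specific Cox models for both events, or a Fine–Gray model for discharge, and say which;
- present these results beside mortality, not alone;
- describe stay separately in survivors and non-survivors, as description only, since restriction to survivors does not remove the problem.

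**Clarifications.** Define 28-day EBPT-free and SETS-free days so that days after death do not count as free, for example a value of 0 for death by day 28. For the paired comparisons, report how many patients died before the after measurement, and describe the result as change among those still alive.

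**Cost.** Mainly a change of wording in the analysis section, and a less familiar effect measure for clinical readers. The Data collection section lists vital status and post-discharge outcome but does not name dates of death and discharge. The planned survival analysis already implies these event times, so it is enough to confirm that the case report form records them.

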**Methods:**

The EROICASS study is a national, non-interventional, multicenter observational prospective cohort study. All consecutive patients with septic shock at participating centers will be prospectively enrolled, with data collection extending from intensive care unit (ICU) admission to hospital discharge. Variables including patient demographics, clinical parameters, EBPT/SETS utilization, and outcomes will be recorded using a web-based data capture system. Statistical analyses will encompass descriptive statistics, hypothesis testing, multivariable regression models, and survival analysis to elucidate the associations between EBPT/SETS utilization and patient outcomes.

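### As written, the plan commits to no severity-adjusted comparison of mortality with and without EBPT: its multivariable models cover treated patients only, and its whole-cohort risk ratio is stratified by AKI alone

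*Protocol article*

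**What the plan says.** The Study aim section and the first item under Secondary outcome set the question: "To assess association between EBPT and 28-day and 90-day mortality in patients with septic shock". The abstract's Methods paragraph says the analyses will include "multivariable regression models, and survival analysis to elucidate the associations between EBPT/SETS utilization and patient outcomes".

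The Statistical analysis plan section of the protocol article then names four things that bear on it:

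- **Group tests.** "Differences between patients undergoing and not undergoing EBPT will be assessed using the chi-square test" for discrete variables, with a t-test or nonparametric test for continuous ones.
- **Multivariable models.** Generalized linear models, with mortality among the outcomes, relate those outcomes to "demographic/clinical variables in patients undergoing EBPT or SETS". Centre characteristics may be added as predictors.
- **Survival analysis.** "Relationships will also be analyzed using survival analysis (Kaplan–Meier approach and Cox proportional hazard models". No population, exposure or covariate is given.
- **Risk ratio.** Mortality at 28 and 90 days is to be assessed by a risk ratio "in the entire population and stratified according to the presence or absence of AKI". SETS is to be handled in the same way.

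The Background says that the decision to start EBPT or RRT often depends on local practice and on the treating physician. The Data collection section lists demographics, comorbidities, APACHE II, SAPS II, SOFA, hemodynamic and perfusion parameters, vasopressor use, KDIGO status, the date and time of ICU admission, and the timing of EBPT and SETS.

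**The concern.** Estimating the association of EBPT with mortality requires treated and untreated patients in the same analysis. The models that the plan calls multivariable exclude the untreated. They can show which treated patients die, but not whether treated patients die more or less often than comparable untreated ones.

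The estimate that does span the whole cohort is stratified by AKI and nothing else. AKI strata remove confounding by AKI status. They leave differences in shock severity, vasopressor need, comorbidity and centre, all of which may drive both the choice of EBPT and death. The Discussion says the study will give clinicians guidance for therapeutic decisions, so an apparent harm or benefit that only reflects who was selected for EBPT would matter.

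**Working it through.** **1. Which analysis reaches the question**

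| Analysis in the plan | Population stated | EBPT yes/no as exposure | Adjustment stated |
|---|---|---|---|
| Group tests | treated and untreated | yes, as grouping | none |
| Generalized linear models | EBPT or SETS patients | not possible for EBPT versus none | demographic and clinical variables, perhaps centre |
| Kaplan–Meier, Cox | not stated | not stated | not stated |
| Mortality risk ratio | entire cohort | implied by context, groups not named | AKI strata only |

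No row combines the whole cohort, EBPT as exposure and severity adjustment. The Cox row could, but the text does not say so.

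**2. Inputs for an illustration**

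The plan gives no figure for the mortality comparison, so none can be reproduced. Taken from the document:

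- 28-day mortality of up to 40% (Background) and EBPT use of 50% (Sample size).
- N = 97 and N = 385 (Sample size). Both follow from Cochran's formula z²p(1−p)/d² with p = 0.5 and absolute d: d = 0.10 gives 96.04, rounded up to 97; d = 0.05 gives 384.15, rounded up to 385.

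Assumed, not in the document: one binary severity factor present in half the patients; mortality 1.5, 2 or 3 times higher when it is present; EBPT uptake of 60/40, 70/30 or 80/20 per cent in severe/non-severe patients; and no effect of EBPT.

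**3. Formulas and central case**

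Let r be the severity risk ratio and a the uptake in severe patients.

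- Non-severe mortality m0 = 0.40 × 2/(1 + r); severe mortality m1 = r × m0.
- Treated mortality = a·m1 + (1 − a)·m0; untreated mortality = (1 − a)·m1 + a·m0.

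With r = 2 and a = 0.7: m0 = 0.267 and m1 = 0.533. Treated = 0.7 × 0.533 + 0.3 × 0.267 = 0.453. Untreated = 0.3 × 0.533 + 0.7 × 0.267 = 0.347. Crude RR = 0.453/0.347 = 1.31 when the true RR is 1.

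The chance of two-sided P < 0.05 is Φ[(δ − 1.96·SE0)/SE1], where δ is the difference, SE0 the pooled standard error and SE1 the unpooled one. With 192.5 per group, δ = 0.1067, SE0 = 0.0499 and SE1 = 0.0496, which gives 0.57. With 48.5 per group it is 0.19.

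**4. Range: crude RR (chance of P < 0.05 at N = 385)**

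| Severity RR | uptake 60/40 | uptake 70/30 | uptake 80/20 |
|---|---|---|---|
| 1.5 | 1.08 (0.093) | 1.17 (0.248) | 1.27 (0.485) |
| 2 | 1.14 (0.186) | 1.31 (0.570) | 1.50 (0.896) |
| 3 | 1.22 (0.360) | 1.50 (0.896) | 1.86 (0.998) |

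If uptake runs the other way, so that sicker patients receive EBPT less often, the two groups swap and each ratio inverts: 0.384/0.416 = 0.92 at one end and 0.28/0.52 = 0.54 at the other. In every cell, adjusting for the severity factor in the whole cohort returns RR = 1.

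**5. Events available for adjustment**

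At 40% mortality, 0.40 × 97 ≈ 39 deaths and 0.40 × 385 = 154 deaths. The Timeline anticipates at least 30 centres, so centre indicators alone would use 30 − 1 = 29 terms, against about 39 deaths at the smaller size.

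**The case against.** The strongest reply is the survival sentence. It carries no restriction to treated patients, and it opens the paragraph that goes on to the whole-cohort risk ratio. A Cox model there could hold EBPT and covariates. The abstract also says that regression and survival models are meant "to elucidate the associations between EBPT/SETS utilization and patient outcomes". Read together, these make the treated-only phrase look like loose drafting. Covariate lists and propensity methods are commonly left to a fuller analysis plan.

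Much of this stands. A reader might infer that the risk ratio is the only mortality analysis of the whole cohort, or that the investigators have decided against adjustment. The document supports neither: the Cox models are left open, the risk ratio is never called unadjusted, and the abstract points towards modelling EBPT use. The missing covariate list is not the point either. What remains is that the article does state a population for its multivariable models, and that population cannot answer the stated aim.

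Two further replies also stand. The treated-only models have a proper use, because Secondary outcome asks for risk factors among EBPT or SETS patients and for the effect of timing. And the mortality question is secondary and worded as a potential association. That wording does not remove the problem, since the abstract and Discussion claim more than description.

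**Conclusion.** The point holds in this form. The stated multivariable models cannot compare EBPT with no EBPT. The only mortality estimate explicitly placed in the entire cohort is stratified by AKI alone, and the Cox sentence is too open to close the gap. The abstract, Secondary outcome and Statistical analysis plan need to be reconciled.

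The size is illustrative. Under no true effect, the unadjusted ratio runs from 1.08 to 1.86 if sicker patients are treated more often, and from 0.92 to 0.54 if they are treated less often. It rests on the assumed severity split, severity effect and uptake, and on 40% as the level of 28-day mortality; the document gives no 90-day figure. The illustration shows that the ratio could mislead in either direction. It does not show that it will, nor which way. The sample size and the primary outcome, the proportion receiving EBPT, are untouched.

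**What to change.** Amend the Statistical analysis plan as follows:

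- State that the 28- and 90-day mortality models are fitted in the whole septic-shock cohort with EBPT as the exposure.
- Treat EBPT as time-varying, or use a landmark. It starts after ICU admission, so a fixed EBPT term in a Cox model counted from admission would credit treated patients with survival time before treatment (immortal-time bias). The admission time and EBPT timing needed for this are already recorded.
- Adjust for a short pre-specified set of ICU-admission covariates already collected, for example age, comorbidity, one of APACHE II or SAPS II, SOFA, vasopressor use and AKI stage, or use propensity weighting on them. Limit the number by expected deaths: about 39 at N = 97 and 154 at N = 385 if mortality is 40%.
- Account for centre by clustering or a random effect, not by many indicator terms.
- Do the same for SETS among patients with renal failure.
- Name the groups compared in the risk ratio and label the unadjusted ratio descriptive.
- Keep the treated-only models for the risk-factor and timing objectives, and say so.
- State that residual confounding remains after adjustment.

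The cost is revised wording and modest analyst time. No new data items are needed for the covariates named.

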#### Study population

##### Inclusion criteria

Septic shock at ICU admission according to sepsis-3 guidelines11Age ≥ 18 years

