### Timeline

The study recruits all consecutive patients with septic shock at the participating centers who will be prospectively enrolled (Fig. 1). Patient enrollment will coincide with ICU admission, and monitoring along with data recording will continue until hospital discharge will be prospectively enrolled. The study duration will be 12 months from the first IRB approval. Prior to the initiation of the study in September 2024, we anticipate that a minimum of 30 centers will be prepared for inclusion. It is noteworthy that the study is scheduled to commence before securing the majority of Institutional Review Board (IRB) approvals.

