### Data management

#### Data collection

Variables will be recorded upon ICU admission and monitored over 72 h, extending to ICU and hospital discharge. The following codified data will be collected via a collection form:Date, time of ICU admission, and originDemographic data and comorbiditiesAPACHE II score, SAPS II score, and SOFA scoreHemodynamic and perfusion parametersUse of vasopressorsConsciousness assessment (Glasgow Coma Score)Blood chemistry tests (platelet count, bilirubin levels, creatinine levels, azotaemia, potassium, sodium, urine quantity)Renal function and definition of renal damage according to KDIGO criteriaTiming, type, and duration of EBPTTiming, type, and duration of SETSVital status during ICU and hospital stayLong-term outcome post-discharge from ICU

The data will be generated and recorded in participating centers via a web application hosted by SIAARTI using REDCap® software. REDCap provides secure, web-based data capture tools with features including the following:Intuitive interface for validated data captureAudit trails for tracking data manipulation and export proceduresAutomated export procedures for data downloads to statistical packagesData integration and interoperability with external sourcesData will be recorded in the e-CRF using coding procedures to comply with data protection laws, including EU GDPR. Each patient will be assigned a unique subject ID for pseudonymized data analysis.

Access to REDCap will be granted only to data collecting staff of participating centers, adhering to outlined procedures. Unauthorized access is prevented through hierarchical, role-based access concepts. Data management and retention will be overseen by SIAARTI, ensuring secure storage accessible only to system administrators. Each participating center will have access only to the patient data it generated and recorded on the REDCap platform. Periodic ad hoc reports on collected data will be provided by each participating center. Measures for de facto anonymization will be established during data collection and processing, eliminating the need for name-related patient identification.

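### The planned 28- and 90-day mortality risk ratios for EBPT carry an immortal-time component favouring EBPT, because they use the whole population enrolled at ICU admission although treatment starts later

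*Protocol article*

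**What the plan says.** All references are to the protocol article.

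- **Entry.** Timeline: "Patient enrollment will coincide with ICU admission". Inclusion criteria: "Septic shock at ICU admission according to sepsis-3 guidelines". Use of EBPT is not part of eligibility.
- **Exposure.** The Background says that the decision to start EBPT rests on local practice and the attending physician. The secondary outcomes refer to values before and after the start and to fluid accumulation at initiation, so the start comes after entry. The sample size section treats EBPT use as a cumulative incidence, that is, a status known only after follow-up.
- **Mortality objective.** Secondary outcome: "To assess association between EBPT and 28-day and 90-day mortality in patients with septic shock". The Study aim also names the association with 90-day mortality.
- **Analysis.** Statistical analysis plan: "Estimates will be used to assess the risk ratio for mortality (at 28 days and 90 days) in the entire population", then by presence or absence of AKI, and "The same approach will be used to assess SETS utilization in the ICU". Kaplan–Meier and Cox models are named without a time origin or a coding for EBPT.
- **Data.** Timing, type and duration of EBPT and SETS are recorded, as are the date and time of ICU admission.

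No landmark, time-dependent exposure or other handling of the delay to treatment is described.

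**The concern.** A risk ratio at a fixed horizon cannot carry an exposure that changes over time. Taken in the entire population it is not a landmark analysis either, since a landmark leaves out the early deaths. What remains is a split by whether EBPT was ever given. Deaths between admission and the intended start then fall in the untreated group, and the treated group is guaranteed to survive to the start. For SETS the same applies to whatever survival its start requires.

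The Study aim includes the association with mortality, and the Discussion expects the results to guide treatment decisions. A ratio below 1 that arises only from the grouping could be read as benefit of a therapy whose effectiveness the Background calls debated.

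**Working it through.** The article gives no figure for the mortality contrast, so there is none to reproduce. The check asks what an ever/never risk ratio shows when EBPT has no effect.

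**Inputs from the article.** 28-day mortality possibly reaching 40% (Background); 50% EBPT use (Sample size).

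**Assumptions.** 46% of patients die, with log-normal death times (median 6 days, log-SD 1.25). This implies:
- death within 24 h: 0.46 × Φ(ln(1/6)/1.25) = 0.46 × 0.076 = 0.035
- death by 28 days: 0.46 × Φ(ln(28/6)/1.25) = 0.46 × 0.891 = 0.41
- death by 90 days: 0.46 × Φ(ln(90/6)/1.25) = 0.46 × 0.985 = 0.453

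Half the patients are destined for EBPT regardless of prognosis. The intended start is log-normal with median m days and log-SD 0.8. EBPT is received only if the patient is still alive.

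**Step 1. Share q of destined patients who die before the start.**
q = 0.46 × Φ(ln(m/6)/√(1.25² + 0.8²)), where the root is 1.484.

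**Step 2. Risk ratio at a horizon with risk r.**
- Ever treated: (r − q)/(1 − q)
- Never treated: (0.5r + 0.5q)/(0.5 + 0.5q) = (r + q)/(1 + q)
- RR = (r − q)(1 + q)/[(1 − q)(r + q)]

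For m = 1 and 28 days: (0.41 − 0.0523) × 1.0523/[0.9477 × 0.4623] = 0.3764/0.4381 = 0.86.

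| Median start (days) | q | RR, 28 days | RR, 90 days | RR, 28 days, all first-24 h deaths removed (simulated) |
|---|---|---|---|---|
| 0.5 | 0.0216 | 0.94 | 0.95 | 0.98 |
| 1 | 0.0523 | 0.86 | 0.88 | about 0.915 |
| 1.5 | 0.0806 | 0.79 | 0.82 | 0.85 |
| 2 | 0.1056 | 0.73 | 0.77 | 0.78 |

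Simulation of the same model agrees with the two middle columns.

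**Step 3. Other assumed death patterns.** Simulation with exponential start times (medians 0.5 to 3 days), half destined for EBPT, no effect:

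| 28-day mortality | Death times | RR, 28 days | RR, 90 days |
|---|---|---|---|
| 40% | exponential | 0.96 to 0.80 | 0.99 to 0.97 |
| 40% | front-loaded (Weibull shape 0.6) | 0.87 to 0.65 | 0.95 to 0.86 |
| 30% | exponential | 0.96 to 0.78 | 0.99 to 0.95 |
| 30% | front-loaded (Weibull shape 0.6) | 0.85 to 0.63 | 0.94 to 0.83 |

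With first-day deaths removed, the 40% rows give 28-day ratios of 0.99 to 0.83 and 0.98 to 0.75. The 90-day shift is smaller here than in Step 2 partly because these curves imply high 90-day mortality: 1 − 0.6^(90/28) = 0.81 for the exponential and 1 − exp(−0.511 × (90/28)^0.6) = 0.64 for the front-loaded pattern at 40%, against 0.453 in Step 2.

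**Step 4. Does a correction recover no effect?** In Step 3's models at 40% mortality, a 72 h landmark gives a 28-day ratio of 0.99 to 1.01 and a time-dependent Cox model gives a hazard ratio of 0.996 to 1.005. In Step 2's model the time-dependent hazard ratio is 0.98 to 1.00.

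**Step 5. Unequal prognosis.** Let eventual mortality be 50.6% in those destined for EBPT and 41.4% in the others (assumed), still with no effect. Without any delay the ratio would be 50.6/41.4 = 1.22. The ever/never 28-day ratio is 1.14, 1.03, 0.95 and 0.87 at median starts of 0.5, 1, 1.5 and 2 days. Divided by 1.22 these are 0.93, 0.84, 0.78 and 0.71, close to Step 2. The immortal-time component is still present, but the net ratio falls on either side of 1.

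**The case against.** **The article is condensed, and exposure coding is usually left to a full plan.** This stands for the survival analyses. A reader might infer that the Kaplan–Meier curves and Cox models also fix EBPT from admission. The text does not say so: a time-dependent Cox model fits its wording, and the sentence follows regression models confined to treated patients. It does not stand for the risk ratios, where horizon and population are both stated.

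**Supporting text can be stretched.** The sentence "Differences between patients undergoing and not undergoing EBPT will be assessed using the chi-square test" concerns comparisons of variables in general and does not name mortality. The objective "To investigate the impact of time of EBPT and SETS on renal outcomes, mortality" might suggest that outcome will be regressed on observed delay, but no method is tied to it. The SETS sentence speaks of utilization; that it covers mortality ratios is inferred from its place after the EBPT ratios and from the secondary objective on SETS and 90-day mortality.

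**The net bias may not favour EBPT.** Correct. A reader might conclude that the study will show a protective association even with no effect. That would need equal prognosis, while the Background leaves initiation to clinical judgement and notes higher mortality in patients with sepsis-associated AKI who need renal replacement. Step 5 shows ratios above 1 with early starts. Two opposing biases do not, however, make a usable estimate.

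**Early deaths are limited by design.** The exclusion for life expectancy under 24 h reduces the component. It is a prediction, so removing every first-day death overstates its effect on those deaths, and even then the 28-day ratio is 0.98 to 0.78. If EBPT starts within hours, little bias remains.

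**Conclusion.** The point holds for the 28- and 90-day mortality risk ratios. As written they include an immortal-time component favouring EBPT, and no safeguard is described. With no effect, equal prognosis and assumed median starts of 0.5 to 2 days, the 28-day ratio is about 0.94 to 0.73 (0.98 to 0.78 without first-day deaths) and the 90-day ratio about 0.95 to 0.77. Other death patterns widen this in both directions. The direction of the component follows from the design; its size rests on assumed start and death times.

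The net direction of the reported association is not determined. The Kaplan–Meier, Cox and timing analyses are underspecified on this point, not shown to be wrong. The primary outcome is untouched.

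**What to change.** 1. Estimate the 28- and 90-day risk ratios from a prespecified landmark: for example, patients alive at 72 h, with EBPT and SETS classified by use up to then. The 72 h point matches a window already in Data collection: "Variables will be recorded upon ICU admission and monitored over 72 h".
2. In any Cox model comparing treated with untreated patients, state ICU admission as time zero and enter EBPT and SETS as time-dependent covariates.
3. Do not show Kaplan–Meier curves by ever/never EBPT from admission.

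**Cost.** Analysis wording only; no new data or patients. The landmark ratio excludes early deaths and applies only to patients alive at the landmark. Under Step 2's assumed death times, 0.46 × Φ(ln(3/6)/1.25) = 0.46 × 0.290 = 0.133 of patients die by 72 h: about 51 of 385, or 13 of 97, and 0.133/0.41 = 32% of the 28-day deaths. Patients who start after the landmark count as unexposed, which dilutes the contrast. The time-dependent Cox model keeps the early deaths and is a useful companion. Neither step removes confounding by indication.
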